## Abstract

**Background:**

Panic disorder (PD) and generalized anxiety disorder (GAD) are two of the most disabling and costly anxiety disorders seen in primary care. However, treatment quality of these disorders in primary care generally falls beneath the standard of international guidelines. Collaborative stepped care is recommended for improving treatment of anxiety disorders, but cost-effectiveness of such an intervention has not yet been assessed in primary care. This article describes the aims and design of a study that is currently underway. The aim of this study is to evaluate effects and costs of a collaborative stepped care approach in the primary care setting for patients with PD and GAD compared with care as usual.

**Methods/design:**

The study is a two armed, cluster randomized controlled trial. Care managers and their primary care practices will be randomized to deliver either collaborative stepped care (CSC) or care as usual (CAU). In the CSC group a general practitioner, care manager and psychiatrist work together in a collaborative care framework. Stepped care is provided in three steps: 1) guided self-help, 2) cognitive behavioral therapy and 3) antidepressant medication. Primary care patients with a DSM-IV diagnosis of PD and/or GAD will be included. 134 completers are needed to attain sufficient power to show a clinically significant effect of 1/2 SD on the primary outcome measure, the Beck Anxiety Inventory (BAI). Data on anxiety symptoms, mental and physical health, quality of life, health resource use and productivity will be collected at baseline and after three, six, nine and twelve months.

**Discussion:**

It is hypothesized that the collaborative stepped care intervention will be more cost-effective than care as usual. The pragmatic design of this study will enable the researchers to evaluate what is possible in real clinical practice, rather than under ideal circumstances. Many requirements for a high quality trial are being met. Results of this study will contribute to treatment options for GAD and PD in the primary care setting. Results will become available in 2011.

**Trial registration:**

NTR1071

## Background

Anxiety disorders are a great burden for patients, the general health system and society as a whole. Patients having an anxiety disorder suffer from considerable disability and reduced quality of life [1]. In addition, anxiety disorders are associated with significant costs due to the use of health services and reduced productivity [2].

Of the anxiety disorders, panic disorder (PD) and generalized anxiety disorder (GAD) are the most disabling [3] and costly [4-6] anxiety disorders that are frequently seen in primary care. Research has indicated that four to seven percent of primary care attendees suffer from one or both of these anxiety disorders [7-10].

As the majority of these patients is only seen in primary care [6,11], this may be a convenient setting to treat these disorders. Treatment for PD and GAD can be highly effective [12,13]. In recent decades the evidence for the effectiveness of treatments for anxiety disorders has been reviewed and described in clinical guidelines for treatment, where cognitive behavioral therapy as well as prescription of antidepressants are considered as first choice of treatment for PD and GAD [14-16]. However, these guidelines are rarely adhered to in primary care. About one third of patients with an anxiety disorder treated in primary care receive appropriate treatment as defined by a minimal accordance with existing guidelines [6,17,18].

One of the reasons for the low quality of treatment is poor recognition of anxiety disorders. Even when compared to depression, the recognition rate of anxiety disorders is low, with about one third of anxiety disorder patients labeled as such by their general practitioner (GP) [19-21]. Several factors are involved in this low recognition rate, such as patients unwillingness or inability to discuss their anxiety problems with their GP [11,22,23] and limited knowledge of GPs about psychiatric disorders. Moreover, GPs frequently work under time pressure and perceive they have not enough time to enquire about emotional problems. In conclusion, competing demands of the patient, the GP and the primary care structure of acute episodic care make diagnosing mental health problems difficult [24].

Although ameliorating recognition of anxiety disorders is necessary [25], it is not sufficient for improving primary health care for these patients [26-28]. GPs often feel they do not have the necessary capabilities to treat these problems [23,29]. Moreover, the primary care system does not seem to be well organized for care for anxiety disorders [25]. As anxiety disorders often have a chronic nature [30], they make a poor fit with the acute disease model of primary care [10]. Therefore, several researchers have proposed to use a chronic care model to implement evidence based care into practice. The most promising of these strategies are based on Wagner's model of care for chronic diseases [31]. This model was originally developed to improve treatment for chronic diseases like diabetes. The strategies following Wagner's model involve collaborative disease management with a pivotal role for a "care manager", who coordinates care, works according to an evidence-based treatment protocol, monitors treatment response and actively follows the patient. This care manager usually is a non-physician professional, who works in close collaboration with the GP. Care manager and GP are further assisted by a specialist from secondary care. This model was adopted for use with mental disorders, with a nurse practitioner or a psychologist as care manager and a psychiatrist functioning as consultant specialist [32,33].

This collaborative care model has been tested extensively in the treatment of depression, showing robust positive results [34,35]. A few studies in the United States have investigated the effectiveness of collaborative care for anxiety disorders, especially PD [36-38] and GAD [37]. When compared to other strategies for improving care for anxiety disorders in ambulatory care, collaborative care seems to be the most effective [39]. In two of the studies described above a cost-effectiveness analysis was performed. In both studies, collaborative care was more effective than care as usual. Results regarding cost effectiveness were inconclusive, with collaborative care being either more or less costly than care as usual [40,41]. Researchers of these collaborative care trials [36] and international guidelines [15] recommend a stepped care approach for mental health care in primary care, with least invasive and costly interventions preceding more invasive and expensive forms of care. Such an approach may make collaborative care interventions more cost-effective.

This article describes the aims and methods of a randomized controlled trial to test the effectiveness of a collaborative stepped care intervention for PD and GAD in primary care in the Netherlands. Such a study is warranted for two reasons. First, there has been no study on the cost-effectiveness of a collaborative care intervention for anxiety disorders that includes a stepped care approach. Second, published studies about collaborative care for anxiety disorders all stem from the United States (US), where the collaborative care model was originally developed. As there are significant differences across health care systems in the US and in European countries [42], the results of the collaborative care studies might not be generalized to other countries without consideration. To fill this gap in research, we designed a collaborative stepped care intervention for GAD and PD in the primary care setting. The treatment algorithm is built up from three interventions that have separately been proven effective and feasible in the primary care setting [29,43]. The interventions consist of guided self help, cognitive behavioral therapy, and antidepressant medication [43]. Other elements of collaborative care include a trained care manager (a mental health practice nurse or psychologist) who coordinates care and provides psychological treatment, the availability of a consultant psychiatrist for advising GP and care manager, telephone follow-up by the care manager and monitoring of anxiety symptoms to evaluate treatment progress and outcome. Effects and costs of the interventions will be assessed and an economic evaluation will be performed to estimate cost-effectiveness and cost-utility of the intervention. All relevant costs to society associated with the burden of anxiety disorders will be taken into account. In accordance with the outcomes of similar previous studies, it is hypothesized that the collaborative stepped care intervention will be at least more effective and possibly less expensive than care as usual.

## Methods/Design

### Objectives

The primary aim of this randomized controlled trial (RCT) is to evaluate the effectiveness of collaborative stepped care (CSC) versus care as usual (CAU) in the treatment of panic disorder (PD) and generalized anxiety disorder (GAD) in primary care, with severity of anxiety symptoms as primary outcome measure. The secondary aim is to evaluate cost-effectiveness (costs of the intervention weighed against a reduction in anxiety symptoms) and to estimate cost-utility (costs of the intervention weighed against gained Quality Adjusted Life Years (QALY's)).

### Study design

The study design is a two-armed, cluster randomized, controlled trial.

### Time frame

This study was initiated in 2008 and will take three years. Results are expected in 2011.

### Recruitment of GPs, care managers and psychiatrists

The study is designed in cooperation with the Netherlands Institute of Mental Health and Addiction (Trimbos Institute), the Department of General Practice and Psychiatry of the VU University Medical Centre in Amsterdam and the Department of Public Health and Primary Care of the Leiden University Medical Centre. GPs in the Leiden region that are located in the region of a large mental health centre (*Rivierduinen*) will receive an invitation to participate in the study, after which a researcher (AM) will contact all practices by phone to recommend participation. Participating practices will be able to decide which professional (e.g. a psychologist, a mental health practice nurse or a social worker) will fulfill the role of care manager. If the practice does not have such a professional available, a mental health practice nurse working at the regional mental health centre will be available to work in the practice. Experienced psychiatrists working at the regional mental health centre will perform as consultant psychiatrists for the intervention practices.

### Randomization

Cluster randomization will be applied at the level of the care manager to minimize contamination of the effect [44]. Randomization will be performed using sequences obtained with an automated random sequence generation algorithm following a blocking scheme of variable length with allowance for restricted unbalance of at most three. Stratification will be on region, with six regions in total, which are based on working units of the regional mental health centre. The allocation sequences will be generated by an independent statistician (HA) in the manner described above. The care managers will be randomized and allocated to the intervention (CSC) or the control group (CAU). PCPs and GPs will be allocated to either CSC or CAU in accordance with the randomization status of their care manager. After randomization, neither care managers nor GPs will be blinded to group assignment. Figure 1 presents a flowchart of the recruitment and randomization procedure.

**Figure 1 F1:**
[figure not shown]
**Flowchart showing the recruitment and randomization of care managers and practices**. GP: general practitioner, PCP: primary care practice, CM: care manager.

### Patient inclusion and exclusion criteria

Patients with a primary diagnosis of PD with or without agoraphobia and/or a primary diagnosis of GAD according to the criteria of the DSM IV [45] will be included in the study. Patients who are suicidal, suffer from dementia or other severe cognitive disorders, psychotic disorder, bipolar disorder, dependence on drugs or alcohol, or with an unstable severe medical condition as diagnosed by their GP or as assessed in a diagnostic interview will be excluded. Patients with insufficient knowledge of the Dutch language to fill out the questionnaires, patients who are already receiving intensive psychological treatment (>2 contacts per month with a psychologist or psychiatrist) and patients who are under 18 years of age will also be excluded from the study. For reasons of generalization, no other exclusion criteria are used. Having received treatment for anxiety problems in the past, using medication (e.g. antidepressants or benzodiazepines) or a diagnosis of co-morbid psychiatric and medical conditions (except for those described above) will not be reasons for exclusion.

### Recruitment of patients

Recruitment of patients will take place in two phases: a screening phase and a diagnostic phase. Patients will either be referred by their GP or will receive an invitation to participate based on a selection of the electronic medical record system of the GP. Patients are blinded for randomization status until they have returned the baseline questionnaire.

### Screening phase

GPs are able to refer a patient by handing a patient an information letter, an informed consent form and a short screening instrument: the Patient Health Questionnaire anxiety subscale (PHQ22) [46]. This measure has shown good psychometric properties for screening for anxiety disorders [46,47].

In cluster randomization, when dependent on referrals of GPs, a known problem is the inclusion of patients in the CAU group [48]. To diminish recruitment bias, referral by GPs is complemented with selection on basis of screening in this study. A number of patients will be selected from the electronic medical records of the GPs according to the following criteria: they are older than 18 years of age and had contact with their GP in the past four months for one of the following reasons: psychological or social problems, muscle or skeletal pain, fatigue, hyperventilation, fainting, stomach ache, complaints about functioning of the heart or head ache. These patients will receive an information letter, an informed consent form and the PHQ-22. Of patients who return the PHQ-22 and give informed consent, the score on the PHQ-22 will be calculated. Patients will be considered screen-positive if they answer affirmatively to the screening questions of the PHQ22 and list at least 4 symptoms for panic or at least 1 symptom for general anxiety [46]. For PD, threshold criteria will be used [49], where as for GAD the sub threshold criteria will be used to increase sensitivity [50]. Screen-positive patients will enter the diagnostic phase and will be contacted by telephone to perform a diagnostic interview.

### Diagnostic phase

Diagnostic interviews will be conducted by trained research assistants who will be blind to the randomization scheme. The MINI-PLUS International Neuropsychiatric Interview is a semi-structured interview that is often used for DSM-IV classification [51,52]. Telephone administered psychiatric interviews are found to have a high concordance with in-person interviews [53]. The interviewers will have the opportunity to consult a psychiatrist, who is also blind to randomization status, when they are uncertain of a diagnosis. Patients with a primary diagnosis of PD and/or GAD and who do not meet any of the exclusion criteria will receive a second information letter, baseline questionnaires and a second informed consent form. Patients will be offered the choice of a pen and paper version or an internet based version of the questionnaire. If the patient returns the baseline questionnaires and gives informed consent, the patient will be included in the study. Patients in the CSC group will be invited for a consultation with the care manager whereas patients in the CAU group will be advised to seek contact with their GP for treatment of their anxiety complaints. GPs in the control group will not be notified of the diagnosis of participating patients. Figure 2 shows a flowchart of participating patients.

**Figure 2 F2:**
[figure not shown]
**Flowchart of participants**. GP: general practitioner, PCP: primary care practice, PHQ22: Patient Health Questionnaire anxiety sub-scale, MINI-interview: MINI-International Neuropsychiatric Interview.

### Sample size

The aim of the trial is to detect a clinically relevant difference of 0.5 SD (Cohen's effect size) of CSC versus CAU on the continuous measure of the Beck Anxiety Inventory (BAI) [54]. Sample size calculation is based on scores of 281 primary care patients in the multisite Netherlands Study of Depression and Anxiety (NESDA) [55] with a diagnosis of PD or GAD in the last six months. The mean BAI score in this sample was 16.94, with an SD of 10.49 (range 0-58). Hence, the expected difference between CSC and CAU is 6 points on the BAI. To demonstrate this difference with alpha = 0.05 and a power of 0.90, 64 cases per arm are needed ((1.96 + 1.28)^2 ^*10.49^2 ^*2)/6^2^). Since the average class size (n) is estimated to be 5 and the intraclass correlation coefficient (rho) is expected to be 0.01 [56,57], we apply an inflation factor of 1.04 (inflation factor = 1 + (n-1) × rho = 1 + 4 * 0.01 = 1.04) [58]. To be able to analyze 67 completers per arm and with an estimated 25% loss to follow-up, we aim to include 89 patients per arm.

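### The sample size is justified as detecting 0.5 SD but is calculated for 6 BAI points (0.57 SD); 134 completers give about 81% power, not 90%, for 0.5 SD

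*Protocol article*

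**What the plan says.** The Sample size section opens with the target: "The aim of the trial is to detect a clinically relevant difference of 0.5 SD", measured on the BAI. It takes the mean (16.94) and SD (10.49) from 281 primary care patients with panic disorder or generalized anxiety disorder in an earlier Dutch cohort. From these it draws the conclusion: "Hence, the expected difference between CSC and CAU is 6 points on the BAI".

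The power statement follows: "To demonstrate this difference with alpha = 0.05 and a power of 0.90, 64 cases per arm are needed". The formula printed with it uses 1.96, 1.28, an SD of 10.49 and a difference of 6. An inflation factor of 1.04 (average cluster size 5, intraclass correlation 0.01) takes this to 67 completers per arm, and an allowance of 25% loss to 89 enrolled per arm.

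The Methods/design paragraph of the abstract reports the outcome as: "134 completers are needed to attain sufficient power to show a clinically significant effect of 1/2 SD on the primary outcome measure". It does not mention 6 points.

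**The concern.** The section gives two target effects and treats them as one. With the only SD it supplies, 0.5 SD is 5.2 points, yet 6 points is presented as following from it. Six points would be 0.5 SD only if the SD were 12, and no such SD appears in the document.

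Required sample size varies with the inverse square of the difference, so a small step in the difference moves the number of patients noticeably. This calculation is the only justification given for the trial's size, and the abstract carries just the 0.5 SD version. A reader who combines the two will believe that the trial has 90% power for the effect it calls clinically relevant. If the trial does not show a difference, that reader will think an effect of 0.5 SD was less likely to have been missed than it was.

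**Working it through.** **Inputs** (all from the Sample size section): target 0.5 SD; SD 10.49; difference used 6 points; two-sided alpha 0.05 (z = 1.96); power 0.90 (z = 1.28); inflation factor 1 + (5 − 1) × 0.01 = 1.04; loss to follow-up 25%; 67 completers and 89 enrolled per arm.

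**1. Reproduce the plan's figures.**
- n per arm = (1.96 + 1.28)² × 10.49² × 2 / 6² = 64.2, stated as 64.
- 64 × 1.04 = 66.6, stated as 67.
- 67 / 0.75 = 89.3, stated as 89.

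The arithmetic is right for a difference of 6 points.

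**2. Compare the two targets.**
- 0.5 × 10.49 = 5.245 points.
- 6 / 10.49 = 0.572 SD.

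**3. Power of the planned size.** Effective n per arm = 67 / 1.04 = 64.4. With d the difference in SD units, power = Φ(d × √(64.4 / 2) − 1.96), and √(64.4 / 2) = 5.68.

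| Difference | d | d × 5.68 − 1.96 | Power |
|---|---|---|---|
| 6 points | 0.572 | 1.29 | 90.1% |
| 5.245 points | 0.500 | 0.88 | 81.0% |

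The noncentral t distribution gives 89.6% and 80.4%. If clustering is ignored (n = 67), power at 0.5 SD is 82.5%, so the inflation factor is not the cause of the gap.

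**4. Size needed for 90% power at 0.5 SD.** With the protocol's z values:
- (1.96 + 1.28)² × 2 / 0.5² = 84.0 per arm.
- 84 × 1.04 = 87.4, so 88 completers.
- 88 / 0.75 = 117 enrolled per arm, about 234 in total.

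Unrounded z values with rounding up at each step give 85, 89 and 119 per arm, or 238 in total. Using 6 instead of 5.245 lowers the required number by 1 − (5.245 / 6)² = 24%.

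**5. Could sidedness explain it?** No. The formula uses 1.96, and a one-sided 5% test at 0.5 SD with 90% power would need 69 per arm before clustering, not 64.

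**The case against.** **The 90% is not literally claimed for 0.5 SD.** It is attached to the difference just named, which is 6 points, and for that the calculation is correct. The abstract claims only that power is sufficient, and 81% is above the customary 80%. This stands as a reading of the individual sentences. It does not remove the error: the section derives the 6 points from the 0.5 SD aim, and 0.90 is the only power level in the document.

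**Six points may have its own basis.** The cohort mean of 16.94 less the remission cut-off of 11 is 5.94. The section does not argue this. If it were the basis, the target would still be 0.57 SD and the description as half an SD would still be wrong. Nor is it rounding, since 5.245 rounds to 5.

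**The planned analysis is not the one in the formula.** The protocol plans an intention-to-treat multilevel model over five measurements, which could gain power over a single comparison of completers. As an illustration only, suppose the model adjusted for baseline BAI with an assumed baseline–outcome correlation of 0.3, 0.4 or 0.5 (none is in the document). Power at 0.5 SD would then be about 84%, 87% or 91%. This is fair, and it means the 81% is conditional on the protocol's simple formula. But the sample size section claims no such gain.

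**The practical effect is modest.** The gap is 0.755 points on a 63-point scale, and the design remains reasonable. A null result should in any case be read from its confidence interval. This limits the consequence and supports a correction of wording rather than a larger trial.

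**Conclusion.** The point holds. The document states a target of 0.5 SD and calculates for 0.57 SD, and nothing in it reconciles the two. Under the protocol's own assumptions (SD 10.49, two-sided alpha 0.05, inflation factor 1.04, 67 completers per arm, unadjusted two-group comparison), power is 90% for 6 points and 81% for 0.5 SD. The risk of missing the stated effect is thus about 19% instead of 10%. Restoring 90% at 0.5 SD would need roughly a third more patients, 234 to 238 enrolled instead of 178. The size of the gap depends on those assumptions; the inconsistency does not.

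**What to change.** Keep enrolment at 178 and correct the statement in both places.

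- **Sample size section:** delete the word that presents 6 points as a consequence of 0.5 SD, and write, for example: *67 completers per arm give 90% power for a difference of 6 BAI points (0.57 SD) and 81% power for 0.5 SD (5.2 points).*
- **Choice of target:** if 6 points is the intended target, give the reason it is clinically relevant and stop describing it as 0.5 SD.
- **Abstract:** attach the 134 completers to the same effect and power.

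The cost is wording, plus a less favourable power figure for 0.5 SD. Enrolment, outcome and analysis are unchanged.
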